# 14.0 QUALITY ASSURANCE

A Quality Assurance Associate from FHI will conduct a site visit and evaluation after at least 5 months of study conduct and then again about 6 months before the projected end of the study. The QA Associate will evaluate study systems for quality control, monitoring of the study, documentation of the study, and overall control of the study.

# 15.0 ETHICS AND RESEARCH INTEGRITY

## 15.1 Institutional Review Board Review and Approval

Before initiating the study, the study must be approved in writing by the Institutional Review Board at the site and FHI’s Protection of Human Subjects Committee in accordance with USFDA regulations (21 CFR Part 56). The study will be conducted in accordance with all conditions of approval by the IRBs. The sites will obtain written reapproval of the research by the IRBs at least annually and forward a copy of the review to FHI.

## 15.2 Informed Consent

No participant may be admitted into this study until the Investigator has obtained her legally effective informed consent. An Investigator shall seek such consent only under circumstances that provide the prospective participant with sufficient opportunity to consider whether or not to participate in the study. Informed consent must be obtained without coercion, undue influence, or misrepresentation of the potential benefits or risks that might be associated with participation in the study.

Informed consent encompasses all oral or written information given to the participant about the study and the study materials. This includes the consent form signed by the participant, recruitment advertising, and any other information provided to the participant. All such information that is given to the participant will be in a language that is understandable to her. The information will not include any language in which the participant is made to waive any of her rights or which releases or appears to release the Investigator, the Investigator’s institution, or FHI from liability for negligence.

Informed consent will be documented by the use of a written consent form that is signed by the participant (or the participant’s mark if she cannot sign). A copy of the signed consent form will be given to each participant. The original signed consent form for each participant will be kept in the participant’s study files separate from the DCFs. The consent form must include each of the basic and additional elements of informed consent described in 21 CFR Part 50.25 and must describe each of the risks or discomforts to the participant that have been identified by FHI as reasonably foreseeable.

## 15.3 Participant Confidentiality

The confidentiality of all participants enrolled into this study will be protected to the fullest extent possible. FHI staff, Biosyn staff, FDA personnel, or other individuals authorized in writing by FHI may audit participant’s clinic records. However, study participants should not be identified by name on any DCF or on any other documentation sent to FHI and will not be reported by name in any report or publication resulting from data collected in this study.

## 15.4 Research Integrity

Concern in the United States about the quality of biomedical and behavioral research has led to the establishment of regulations and guidelines for handling the allegations of scientific misconduct.  As a recipient of U.S. government funding, FHI is required to develop policies and procedures related to scientific misconduct that conform to these regulations.  The regulations define "misconduct" in science as a "fabrication, falsification, plagiarism, or other practices that seriously deviate from those that are commonly accepted within the scientific community for proposing, conducting, or reporting research.  It does not include honest errors or honest differences in interpretations or judgments of data (42 CFR 50.102.)

FHI has specific obligations under these regulations with respect to the handling of information related to scientific misconduct that may come to its attention.  In addition, the regulations require that FHI establish procedures related to initiating an inquiry, pursuing an investigation, and informing a specified circle of authorities should the situation warrant it.  FHI will pursue all allegations of misconduct in research or questionable academic conduct that may raise legitimate suspicions of misconduct, and will conduct inquiries and investigations to resolve questions regarding the integrity of research.  In conducting inquiries during an investigation, FHI will focus on the substance of the issue and will be vigilant not to permit personal conflicts between colleagues to obscure the facts.

# 16.0 PUBLICATION POLICY

All information concerning the drug supplied by FHI to the Investigator and not previously published is considered confidential.

The initial publication from this study will be the aggregate multicenter results focusing on the primary endpoints of SAVVY safety and HIV prevention effectiveness. Subsequent secondary analyses and manuscripts, including any single center data, will be agreed upon by members of the protocol team and reviewed by FHI. All suggestions for the manuscript will be returned to the first author by FHI within 15 working days of receiving it.

For publication of the main findings of this study, the Investigator and Study Coordinator from each site, and the Project Leader and Lead Statistician from FHI will be considered as authors (a total of 6 persons). Other key contributors to the research will be acknowledged as part of the Nigeria SAVVY Phase 3 Research Team.

# 17.0 ADDITIONAL INVESTIGATOR RESPONSIBILITIES

In addition to the previously described responsibilities, the Investigator is responsible for signing and dating the cover page of this study protocol. The signed and dated original must be submitted to FHI before protocol implementation, and the Investigator at the site must maintain a copy with the study files.

All protocol amendments must be signed and dated by the Investigator. The signed and dated original must be submitted to FHI before implementation of the amendment, and the Investigator at the site must maintain a copy. Amendments must be approved by FHI and the IRB before implementation.

The Investigator will provide FHI with a curriculum vitae (CV) for himself showing the education, training, and experience that qualifies him as an expert in the area of clinical investigation specific to the product under investigation and his affiliation with the site at which the study is being conducted. CVs also must be provided for all individuals listed as Sub-Investigators on the Form FDA-1572 and the Site Coordinator showing the education, training, and experience that qualifies them for their role in the study, and their affiliation with the study site. If and when any personnel listed on the 1572 changes, the Investigator will notify FHI and provide a CV for any new staff on the form.

The Investigator will supply FHI with copies of the current license and/or laboratory certification (such as the Clinical Laboratory Improvement Act [CLIA] certification) of any laboratory used for the study. The Investigator is responsible for obtaining any updates to these documents and sending them to FHI in a timely fashion. This includes documentation of the normal ranges of the laboratory tests used by the laboratory. The Investigator will ensure that appropriate health care or referral is provided for the study participants throughout the study. Copies of all these documents must be maintained at the site.

Throughout the course of the study, the Investigator will prepare and submit to FHI whatever reports are required and detailed in the Subcontract Agreement to be signed prior to initiating the study. These reports summarize the accomplishments of the assignment and usually include the following:

- all changes in the research activity; and
- all unanticipated problems involving risks to participants or others.

The final technical report will be submitted within 45 days after completion of the study unless this period is extended in writing by FHI.

# PROTOCOL ADDENDUM

**Study 9784: Randomized Controlled Trial of SAVVY and HIV in Nigeria**

Amendment 2

After careful discussion with the manufacturer of SAVVY gel, other microbicide researchers, and women’s health advocates, we will increase the level of safety monitoring for participants in the SAVVY phase 3 trials. Our intensified safety monitoring will involve four activities that obligate a study protocol amendment.

**1. Statistical Monitoring Plan and DMC Review**

The following represents our proposed statistical plan for monitoring the SAVVY trials for a potentially harmful SAVVY effect. However, the final plan is contingent upon review and approval by the sponsor and the members of the DMC.

In addition to the interim analysis for both harm and effectiveness at the study midway point (i.e., after approximately 33 HIV events) as originally planned, we propose to perform a first interim analysis after approximately 16 HIV events have occurred. After 16 events, we will ask that the DMC only consider stopping the study for a potentially harmful SAVVY effect (not because of early evidence that SAVVY is effective). At the study midway point, the DMC will again look for a potentially harmful effect, but we will also allow consideration for stopping the study due to significant evidence that SAVVY is effective at that interim point. The test that we propose to use at the midway point will be asymmetric, making it easier to stop for potential harm than for effectiveness.

For each of the two interim analyses, we propose to use a more liberal significance level (e.g., 0.10) to test for a potentially harmful effect. Statistical simulations and power calculations show that conducting a one-sided test for harm at the 0.10 significance level at each of the two interim analyses would have the following properties/operating characteristics:

- would scarcely reduce the power to detect a significant positive effect of SAVVY
- would not inflate the probability of a type I error for effectiveness
- would not increase the necessary study size
- would be able to detect a harmful effect of SAVVY (relative rate = 2) with 55% power at the first interim look (after only 16 HIV events) and with 80% power by the halfway point.

It is important to recognize that the proposed test for a potentially harmful effect will not be likely to offer conclusive evidence that SAVVY is indeed harmful relative to placebo. For example, if SAVVY truly has no effect beyond that of the placebo, then the proposed test at the 0.10 significance level has a 10% probability of concluding "potential harm" at the first look and a 15% chance of concluding “potential harm” at either the first or second look. Thus, before recommending that either study should be terminated early due to interim evidence of a potentially harmful effect, the DMC will likely want to consider the emerging evidence from the other study as well. So, for example, if the interim analysis in the Nigeria study after 16 events resulted in a marginally significant p-value of 0.09 but the interim results from the Ghana study indicated that SAVVY may well be protective, then it may be unwise for the DMC to recommend stopping either study. In addition, the DMC will likely consider other evidence from within each of the studies (such as the distribution of AEs across the treatment arms) before making their recommendation.

In order to maintain the overall one-sided significance level for declaring SAVVY effective at 0.025, we will adjust the effectiveness significance level at the interim and final looks using the Lan-DeMets spending function with O'Brien-Fleming type boundaries, as specified in the protocol. If the interim analysis occurs at precisely the halfway point in terms of number of HIV infections, the one-sided significance levels to test for effectiveness will be 0.0026 and 0.024 at the interim and final analyses, respectively.

**2. Additional Scheduled Testing for Chlamydial Infection**

The USFDA Division of Antiviral Drug Products has expressed concern that we could miss a large number of cervical infections, given that study participants would make their follow-up visits at outreach offices and no regular testing would be scheduled after baseline. That way, only symptomatic (or simply worried) women would be directed to the clinics for STI testing. The Sponsor is not aware of any reliable data to suggest that use of SAVVY increases the risk of chlamydia, and additional clinic visits with pelvic examinations could increase participant burden/fatigue, which in turn might compromise our retention rates and ability to assess effectiveness against HIV acquisition.

To address the USFDA concern without threatening retention unduly, we propose to test each study participant one more time during the study, at or after her six-month observation point. The chlamydia testing requires a cervical swab and thus a clinic visit. With the large number of women in this study, we will have 80% power to detect a roughly 5% difference in prevalence using a logistic regression model that adjusts for baseline STI status.

The Sponsor is not aware of any reliable data indicating reduced test performance in the presence of SAVVY gel. In addition, the characteristics of the gel substance would not be expected to interfere or cross react with the antigen capture technology employed in the study chlamydia test. However, the sponsor has decided to perform further validation studies of chlamydia test performance in the presence of study gel to yield additional data on the accuracy of such testing.

The follow-up chlamydia data, and the information on chlamydia test performance, will allow us to evaluate whether women in one of the study arms have a higher prevalence of chlamydial infection, a possible indicator of harm. These data will be made available to the DMC, along with the HIV incidence data and information on other adverse events (AEs).

1. **Ascertainment of Pregnancy Outcomes**

We know that a number of pregnancies will occur during the SAVVY studies. We will counsel women who become pregnant to stop using the gel, although they will be encouraged to continue making follow-up visits. We have not included items on pregnancy outcomes on our data collection forms. The FDA has asked Biosyn to supply data on outcomes of pregnancies occurring while women are using study product.

In response, we will design a worksheet to capture information on the pregnancy outcomes. The worksheet will not be a data collection form entered into the data base, but rather a simple single sheet for each pregnancy. This task will be done by the outreach workers. In some cases, outcome data will be collected at routine follow-up visits. In other cases, outreach workers will have to make home visits for a pregnancy outcome interview. We will summarize these outcomes for all participants who become pregnant during the study.

We will develop a financial arrangement that allows some outreach workers to be retained on staff long enough to follow all of the pregnancies that occur during the study, even those that end after the trial is finished.

1. **Adverse Event Monitoring**

In addition to the above protocol changes, we will monitor quarterly or more frequently all adverse events (AEs) entered in the Ghana and Nigeria study data bases by our web-based data entry procedures. AEs will be coded using the MEDRA system in a collaborative effort by the study clinician and data management staff. AEs will then be summarized by body system, but not by study arm. Incidence and prevalence rates will be calculated, but no statistical comparisons will be made.

These routine AE monitoring procedures are in addition to standard Serious Adverse Event (SAE) reporting that will be performed as required by the protocol, the USFDA, and the IRBs.

Finally, the SAVVY trials will follow revised FHI SOP #301-04 on SAE handling. The main change in this SOP is that SAEs will be directed to Regulatory Affairs and Quality Assurance (RAQA) staff first, in an effort to speed the assessment and reporting of SAEs to the sponsor and the USFDA. Study staff will be trained to use the updated SAE fax cover sheet and to direct the SAE reports to the RAQA fax machine.

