## 3.2 Study Design

This is a Phase 3 multi-center, randomized, fully-masked, placebo controlled trial to assess the effectiveness of 1.0% SAVVY in preventing male-to-female vaginal transmission of HIV infection among women at high risk. Eligible participants who are HIV negative, at risk of becoming infected, and are willing to use a vaginal microbicide each time they have intercourse throughout 12 months of study participation will be recruited in Lagos and Ibadan, Nigeria. Approximately 2,142 participants will be enrolled: half of the participants using 1.0% SAVVY with male condoms and the other half using placebo with male condoms. The enrollment phase will last 12 months or until enough participants are enrolled to yield at least 66 new HIV infections.

Enrolled participants will be randomized into either the SAVVY or placebo arm in a 1:1 allocation ratio. Participants will have monthly follow up visits. At each visit they will:

- Receive additional study product
- Undergo a structured interview
- Give urine for a pregnancy test
- Receive HIV risk reduction counseling and
- Give an OMT specimen for HIV testing.

All women will be counseled to use condoms every time they have intercourse to minimize HIV/STI transmission. Participants will also receive contraceptive counseling and referral during screening and enrollment, and may use any additional non-vaginal contraceptive of their choice, although none will be provided as part of this study.

Participants who are HIV-positive at screening or enrollment, or who acquire HIV infection during follow-up, will be counseled and referred to the appropriate medical services.

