## 3.3 Measures to Minimize Bias

### 3.3.1 Randomization

A Randomization Manager who is not otherwise involved with the study will develop the allocation sequence using a computer random number generator and randomly varied permuted-blocks. Participants will be randomized to one of six groups (three will be SAVVY and three will be placebo) only after they have qualified for the study and signed the enrollment consent form. Randomization will be stratified by study site and each site will have its own list.

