# 9.0 STATISTICAL SUMMARY

## 9.1 Study Size Justification

A two-sided log-rank test with an overall sample size of 2,142 participants (of which 1,071 are in the SAVVY group and 1,071 are in the placebo group) achieves at least 80% power at a 0.05 significance level to detect a 50% reduction in the HIV infection rate if the rate of infection in the control group is 5/100 person-years and loss to follow-up is at most 20% in both groups. These calculations were conducted using the PASS 2000 software, which assumes exponential models for the times to HIV detection and losses to follow-up. Approximately 66 total HIV infections are required to achieve the desired power.

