### 9.2.1 Analysis of effectiveness outcomes

The effect of SAVVY on the time to HIV detection will be determined using two one-sided log-rank tests stratified by site. The type one error rate for the one-sided test with alternative hypothesis that SAVVY protects against HIV acquisition will be carried out at the 0.025 level and adjusted to account for the interim analysis described below.[[1]](#footnote-2) Secondarily, proportional hazards regression models will be used to estimate the hazard rate ratio, along with a 95% confidence interval, comparing the SAVVY group to the placebo group for the HIV outcome, controlling for site and any important baseline prognostic variables. A list of the baseline prognostic variables to be included in the models will be provided in the detailed analysis plan prior to study initiation. The homogeneity of the treatment effect across sites will be investigated by introducing a treatment-by-site interaction term to the model. Crude incidence rates, rate ratios, and 95% confidence intervals will be calculated and will be based on the ratio of the number of new infections to the total length of treatment exposure in the interval. Time to HIV detection, in days, will be computed as the difference between the date of HIV detection, estimated using the midpoint between the dates of the first positive HIV test and the preceding negative HIV test, and the enrollment date, plus one.

In addition to the primary analysis, Investigators have an interest in comparing pregnancy rates between the SAVVY and placebo groups. Crude pregnancy rates and corresponding 95% confidence intervals will be calculated by randomization group, and stratified by contraceptive method used at baseline. Outcomes of all pregnancies that occur will be ascertained on worksheets designed for that purpose (see Protocol Addendum, p.37). No hypothesis tests regarding pregnancies are planned. Because this is not a study of the contraceptive effectiveness of SAVVY and because participants will not be discontinued after they develop a desire to become pregnant during the study, any results regarding this outcome will be interpreted with extreme care.

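### The chlamydia model named in the addendum leaves out site, the randomization stratum; adding it is a small, free improvement that makes the harm comparison slightly less conservative.

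*Protocol*

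**What the plan says.** Item 2 of the Protocol Addendum (Additional Scheduled Testing for Chlamydial Infection) proposes to "test each study participant one more time during the study, at or after her six-month observation point". It says of the resulting comparison that "we will have 80% power to detect a roughly 5% difference in prevalence", and the method given is "using a logistic regression model that adjusts for baseline STI status". Baseline STI status is the only covariate mentioned. A higher prevalence in one arm is treated as a possible sign of harm, and the data go to the DMC. No significance level or stopping boundary is attached.

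Section 3.3.1 states: "Randomization will be stratified by study site and each site will have its own list". There are two sites, since women "will be recruited in Lagos and Ibadan, Nigeria".

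Section 9.2.1 carries the stratum into the HIV analyses. The primary analysis uses "two one-sided log-rank tests stratified by site", and the proportional hazards model controls for site as well as baseline prognostic variables. That section leaves the list of further covariates to the detailed analysis plan, but it names site itself.

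**The concern.** The protocol names a model for two between-arm outcomes, HIV and chlamydia. Site is in the first and not in the second, and no reason is given. When allocation is balanced within site and the outcome differs between sites, an analysis that ignores site counts between-site variation as chance variation between the arms. The stratified design has already removed that variation, so the test rejects a little less often than its nominal level. For a harm signal this is the less welcome direction: a real excess on SAVVY is slightly easier to miss. Elsewhere the addendum deliberately makes the HIV harm tests liberal (one-sided 0.10), so a conservative harm comparison for chlamydia sits awkwardly beside them.

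**Working it through.** **Inputs from the protocol.** "1,071 are in the SAVVY group and 1,071 are in the placebo group" (section 9.1); loss to follow-up of at most 20% (section 9.1), so 1,071 × 0.80 ≈ 857 per arm; women "randomized into either the SAVVY or placebo arm in a 1:1 allocation ratio" (section 3.2); two sites; 80% power for a difference of about 5%, read as 5 percentage points.

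**Assumptions, because the protocol is silent.** Chlamydia prevalence overall and by site, two-sided 0.05, two sites of equal size.

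**1. The plan's own figure.** Power = Φ[(δ − 1.96·√(2p̄(1−p̄)/n)) / √((p0(1−p0)+p1(1−p1))/n)].
- n = 857, 14% v 19%: (0.05 − 1.96 × 0.01793)/0.01789 = 0.83, so power is 0.797.
- n = 1,071, 19% v 24%: power is 0.805.
- Control prevalence from 5% to 30%: power runs from 0.976 to 0.599 (n = 857) and from 0.993 to 0.695 (n = 1,071).

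The 80% is plausible. It can be neither confirmed nor refuted without the control prevalence.

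**2. Overstatement of the standard error without site, under no treatment effect.** The ratio of the standard error used to the true sampling SD is r = √[p̄(1−p̄) / mean within-site p(1−p)]. Type I error is 2[1 − Φ(1.96r)].

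| Site prevalences | p̄(1−p̄) | Mean within site | r | Type I error |
|---|---|---|---|---|
| 10% v 10% | 0.0900 | 0.0900 | 1.000 | 0.050 |
| 5% v 15% | 0.0900 | 0.0875 | 1.014 | 0.047 |
| 5% v 25% | 0.1275 | 0.1175 | 1.042 | 0.041 |

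Simulated logistic models (857 per arm, no baseline STI term) agree: the excess was about 1–2% at 5% v 15% and 4–5% at 5% v 25%, with type I error 0.045 and 0.040.

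**3. Power for a 5-point excess, 857 per arm.** Let V = [p0(1−p0)+p1(1−p1)]/n, and Vs = V − 2·(gap²/4)/n once site is accounted for. Power without site is Φ[(0.05 − 1.96√V)/√Vs]; with site it is Φ[0.05/√Vs − 1.96].
- 5% v 15% (overall 10% v 15%): nV = 0.2175, nVs = 0.2125, √V = 0.01593, √Vs = 0.01575. Power is 0.883 without site and 0.888 with it, a gain of about 0.4 points.
- 5% v 25% (overall 15% v 20%): nV = 0.2875, nVs = 0.2675, √V = 0.01832, √Vs = 0.01767. Power is 0.788 and 0.808, a gain of about 2.0 points.
- Equal sites: V = Vs, so the gain is zero.

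The simulation in step 2 gave gains of about 0.3 and 2 points. A second simulation, around 14% v 19% with baseline STI in both models, gave 0.8 points at a 10-point site gap and 3.1 at a 20-point gap. Power without site stayed at 0.81–0.82 in that simulation.

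**4. What happens on the log-odds scale (second simulation).**

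| Site gap | Without site: log OR / SE | With site: log OR / SE | z without | z with |
|---|---|---|---|---|
| 10 points | 0.3776 / 0.1338 | 0.3881 / 0.1357 | 2.82 | 2.86 |
| 16 points | 0.3765 / 0.1336 | 0.4040 / 0.1385 | 2.82 | 2.92 |

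Adding site raises the reported standard error. The log odds ratio, now conditional on site, moves further from zero by a larger proportion, and the test gains from that. The narrower interval appears for the prevalence difference, as in step 3.

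**The case against.** The strongest objection is that the addendum sentence is a power statement and not a full model specification. It does not say that the covariate list is complete or that site is excluded, and section 9.2 leaves detail to an analysis plan that is not shown. This stands in part: there is no contradiction here and no proven omission from the final analysis. But the sentence does name the model and its adjustment and defers nothing, whereas section 9.2.1 defers its covariate list and still names site. A statistician working from the addendum would fit the model without the stratum.

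A second objection is that the effect is small and conditional. This stands. The documents give no prevalence by site, the loss is zero if the sites are alike, and baseline STI status would absorb some of any site difference. The comparison is also supportive, since section 9.3.2 bases early stopping primarily on HIV event rates.

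A third objection is that adding a prognostic covariate to a logistic model widens the standard error of the treatment coefficient. This also stands, as step 4 shows. A reader might infer from the missing term that the odds-ratio interval is too wide and that adding site would narrow it. It would not. The standard error without site is too large only relative to that estimator's own sampling variability under stratified allocation.

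**Conclusion.** The point holds as a minor improvement. The one chlamydia model that the protocol names omits the randomization stratum, and the HIV analyses include it. If prevalence differs between the cities, the chlamydia test is slightly conservative. For assumed prevalences of 5% v 15% to 5% v 25%, with equal sites, 857 women per arm and two-sided 0.05, the standard error is about 1–5% above the true sampling variability. The cost is about 0.3 to 2 points of power before the baseline STI term recovers part. The second simulation puts the upper end near 3 points at a 20-point gap. With equal site prevalences the cost is nil.

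A reader might go on to infer that the stated 80% power is wrong or that the harm comparison is invalid. Neither is supported. The 80% is attainable at plausible prevalences without site in the model, and any error from leaving site out lies on the conservative side.

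**What to change.** In item 2 of the addendum, describe the model as *logistic regression adjusting for site and baseline STI status*. Add that the site-adjusted difference in prevalence will be reported with its 95% confidence interval, because the stated target is a difference in prevalence and that is the scale on which the precision gain is visible.

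The cost is a few words for the model and one more reported estimate. Site is known for every woman because each site has its own randomization list. No extra data, visits or participants are needed.
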